### Recruitment

Potential participants will be recruited in two ways. Firstly, the health records of elderly people in each participating rural community health service center will be reviewed by a trained project field officer. Secondly, referrals from health professionals and family caregivers will be used as a strategy to recruit participants. Appropriate family caregivers will be notified of opportunities to join this program and a full explanation will be provided. Family caregivers who meet the inclusion criteria and would like to participate in the program will be contacted by a project field officer to set up an initial meeting. During the enrolment meeting, written materials about this program and their rights and risks as a participant will be provided and written informed consent will be obtained. All family caregivers will be informed that they can withdraw at any time. We will also document the reasons why caregivers refused to participate in the study. The research team will use a de-identifiable form to collect the information provided by participants. All collected information will be treated anonymously and confidentially. The selection process and the anticipated number of participants is shown in Fig. 1.

**Fig. 1 Fig1:**
[figure not shown]
Flow-chart of sample framework and number of participants in the project

### Randomization and allocation concealment

A randomization protocol will be used to select fourteen community health service centers in Hanshou County randomly (http://stattrek.com/statistics/random-number-generator.aspx). There will be seven centers in each group (intervention group and control group). An external biostatistician who will not participate in the study intervention or data analysis will conduct the randomisation. All eligible family caregivers living in the intervention communities will be the intervention participants, while those living in the control communities will be control participants.

### Blinding

Because randomisation will occur at the level of individual centers, individual participants will not be blind to the condition they will receive. The researchers and statisticians responsible for data collection and analysis will be blinded regarding group assignments. Only the team member conducting the intervention will be informed of group assignments given the nature of the intervention.

### Intervention

Three theoretical approaches inform the ITBCS program. First, Ruth Cohn’s theme-centered interaction (TCI) model that emphasizes partnerships with family caregivers to improve their self-management of dementia at home and thereby reduce difficult behaviours of people with dementia [30]. Second, the perspective of systemic therapy that emphasizes psychological burdens should not just be considered at the individual level, but also at the system level where people with dementia are cared for [31]. Third, the principles of behavioral therapy point out that difficult behaviours of people with dementia could be triggered by the behaviour of their family caregivers [32]. Therefore, coaching caregivers to apply evidence-based care approaches can reduce difficult behaviours and caregiver burdens. The ITBCS program is designed to enhance family caregiver coping abilities through active problem-solving and facilitating positive changes within the family system via individual phone care support sessions.

Participants will be enrolled for 15 months. For intervention and control groups, there are four assessment time points: the beginning of the study (T-0) and at 3 months after baseline (T1), 9 months after baseline (T2), and 15 months after baseline (T-3). The assessment time points and intervention activities for both groups is shown in Table 1. The ITBCS program includes two major components: intensive ITBCS intervention and telephone consultations at the maintenance phase.

**Table 1 Tab1:**
[figure not shown]
Intervention activities timeline

P-1: Initial orientation talk; P-2: Education booklet delivery; P-3: Theme 1 introduction; P-4: Theme 1 evaluation; P-5: Theme 2 introduction; P-6: Theme 2 evaluation; P-7: Theme 3 introduction; P-8: Theme 3 evaluation; P-9: Theme 4 introduction; P-10: Theme 4 evaluation; P-11: Theme 5 introduction; P-12: Theme 5 evaluation

F-1 to F-6: Monthly follow-up consultations

C-1 to C-3: Telephone-based follow-up to improve compliance

T-0 to T-3: Data collection

#### Intensive ITBCS intervention

Each family caregiver will receive 12 telephone contacts distributed over 3 months that focus on five care support themes. The objective and content of each theme is shown in Table 2.

**Table 2 Tab2:** Care support theme and content

Theme	Objective	Content
1. Caregiver Burden	Provide knowledge about the negative influence of stress. Strengthen family caregivers’ skills in managing the care burden.	• Provide education on caregiving, stress, and safety. • Teach stress management strategies: for example, stretching exercises, breathing exercise.
2. Difficult behaviours	Enhance family caregivers’ ability to manage difficult behaviours.	• Provide knowledge about dementia symptoms. • Provide step-by-step strategies to manage specific difficult behaviours. • Conduct brainstorming of difficult behaviours management strategies.
3. Depression	Provide skills in mood management. Enhance family caregivers’ psychological well-being.	• Provide knowledge about the importance of psychological well-being. • Teach family caregiver how to engage in pleasant events. • Teach family caregiver how to manage mood. • Establish a schedule of pleasant events.
4. Self-care and healthy behaviours	Enhance family caregiver’s physical well-being and teach self-care behaviours	• Provide knowledge about preventive health practices and self-care. • Teach healthy behaviours (e.g., physical exercise, sleep, nutrition, adherence to prescribed medication)
5. Social support	Enhance family caregiver’s social support, and care support	• Provide knowledge about the importance of social support. • Teach family caregiver to access community resources and refer to resource guide. • Teach communication skills with health professionals and other family caregivers • Strengthen participation of telephone-based support sessions.

The intensive ITBCS intervention consists of four steps.*Step 1 Orientation talk:* In order to address the concerns of each family caregiver during the structured care support sessions (step 3), the project field officer should have an understanding of their particular care situation. Therefore, at the beginning of the intervention, the project field officer will conduct an orientation telephone conversation with each family caregiver (lasting around 30 min). In addition, the ITBCS program process and conversation rules will be discussed. There will be four project field officers in each center and each project field officer will be assigned three family caregivers.*Step 2 Education booklet delivery:* To support the thematic introduction of each care support session (step 3), the research team will develop an education booklet summarizing information on the five support themes and listing project field officer contact details for family caregivers. This booklet could also be used as a care diary during support sessions. Each participating caregiver will receive a copy.*Step 3 Structured care support sessions:* Each family caregiver will receive five telephone-based care support sessions delivered by a project field officer. Support sessions will be scheduled to occur every 2 weeks. The duration of a support session is about 60 min. At the beginning of a support session, one of five care support themes will be introduced and discussed for around 30 min. After the thematic discussion, the remaining 30 min will be available for a discussion between the project field officer and family caregiver in order to solve individual problems within this support theme and better utilise family resources. Table 3 outlines an exemplary structure of a care support session.*Step 4 Structured evaluation of each care support session:* In the week after each care support session, a project field officer will conduct a structured telephone-based interview with each family caregiver. The semi-structured questions include the following: What was good? What did you benefit from this session? What did you miss, and do any questions remain unanswered? Which issues do you want to add to the next session?

**Table 3 Tab3:** An exemplary structure of a care support session

(1) Brief review of the previous session content and identification of any changes since then. Introduce the focus of this session and how it will be structured.	
(2) Detailed introduction of the care support theme.	
(3) Check and evaluate of usage of the information and strategies in the information booklet.	
(4) Provide training or education to help family caregivers solve problems and better use family resources.	
(5) Identify and initiate a problem-solving approach focusing on the caregiver’s individual problems and risk behaviours.	
(6) Closure: • briefly review problem areas. • briefly review strategies. • emphasise the importance of implementation strategies in daily care practice. • establish date and time of next session.	

#### Maintenance telephone consultation session

After the intensive ITBCS intervention, participants will receive monthly maintenance telephone consultation sessions for 6 months. A project field officer will conduct the maintenance telephone consultation. Each consultation lasts no more than 20 min.

#### Train the trainer

The current study uses a train the trainer model to increase intervention fidelity and build sustainability of the ITBCS program. Four project field officers in each center will be trained in the ITBCS intervention and carer support skills using a train the trainer model of carer support based on the facilitating guidebook developed by the research team. The responsibilities of project field officers will include: (1) participants recruitment; (2) providing ITBCS to participants; and (3) making reminder telephone calls for the four time-point assessments. The use of the facilitating guidebook will achieve standardization of the intervention delivery.

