#### Treatment as usual for the control group

Participants in the control group will not receive the ITBCS program during the intervention phase. They will continue with usual services available for them during this period without any restriction (usual care). From our previous study in this population, very few family caregivers receive any support outside their family in rural China, so we do not expect this to influence the study outcome. Similar to the intervention group, One GPs and one RN from each community health service center in the control group will be trained as project field officers. Their responsibilities will include: (1) participants recruitment; (2) making telephone reminder calls for the four time-point measurements; and (3) delivering the ITBCS program to participants in the control group after completion of the present study. The participants will complete the same measurements at the same time points as the ITBCS group.

Upon completing the 15-month study, all participants will receive a “thank you” letter for their participation in the study. The study flowchart is displayed in Fig. 2.

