### Intervention fidelity

The ITBCS project field officers will receive 12 hours of training to standardize delivery of the ITBCS program prior to participant recruitment. The research team will support and supervise the project field officers while implementing the ITBCS program. To maintain the intervention fidelity, records will be kept by both project field officers and family caregivers of people with dementia including: (1) intervention record-project field officer version; and (2) intervention record-family caregiver version. Compliance with the intervention protocol will be checked by using these two tools. In addition, the study will have a safety officer (SO). The responsibilities of the SO include, but are not limited to, auditing study processes, maintaining data confidentiality and safety, and contingency planning.

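### As written, the plan implies that caregivers are recruited after their centre's arm is known, in intervention centres by the officers who deliver the programme, so selection within centres is not guarded against

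*Protocol article*

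**What the plan says.** All places are in the Protocol article.

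- **Randomization and allocation concealment.** Fourteen centres are randomised, seven per arm, by an external biostatistician. Arm follows residence: "All eligible family caregivers living in the intervention communities will be the intervention participants, while those living in the control communities will be control participants".
- **Recruitment.** A trained field officer searches the centre's records, and referrals add further caregivers. A field officer then contacts those who are willing and arranges the meeting at which consent is taken.
- **Train the trainer.** "The responsibilities of project field officers will include: (1) participants recruitment; (2) providing ITBCS to participants". On staffing: "Four project field officers in each center will be trained in the ITBCS intervention and carer support skills".
- **Intensive ITBCS intervention.** "There will be four project field officers in each center and each project field officer will be assigned three family caregivers".
- **Intervention fidelity.** The ITBCS officers "will receive 12 hours of training to standardize delivery of the ITBCS program prior to participant recruitment".
- **Treatment as usual for the control group.** "One GPs and one RN from each community health service center in the control group will be trained as project field officers". These officers also recruit and make reminder calls. Their remaining duty is "delivering the ITBCS program to participants in the control group after completion of the present study".
- **Blinding.** Data collectors and analysts are blinded. Whoever conducts the intervention is told the assignment, and caregivers are not blinded. Recruiters are not listed among the blinded staff.

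**The concern.** When individuals enter a cluster trial after their cluster's arm is known, two steps can depend on arm: whom the recruiter finds and approaches, and who agrees. Here an intervention-centre officer recruits caregivers whom the same team will then telephone 12 times over three months and monthly for a further six. A control-centre officer offers assessments now and the programme after the study. Both recruiter and caregiver may therefore behave differently by arm, and referrals leave further discretion.

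At stake is the comparability of the two groups on things the baseline ZBI does not capture, such as motivation, willingness to be called and the course of burden. The outcome is the caregiver's own rating, given without blinding. Intention to treat keeps whatever groups were recruited, so the analysis cannot repair a difference created at enrolment.

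**Working it through.** **1. Order of events, from the sections side by side**

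- A caregiver's arm is fixed once the centre's arm is fixed (Randomization and allocation concealment).
- The control-group section describes choosing and training staff in centres already labelled control, and lists recruitment first among their duties.
- In intervention centres the deliverers recruit (Train the trainer), and their training in delivery comes first (Intervention fidelity).
- Deliverers are told the allocation (Blinding).
- No section places identification, consent or T-0 before allocation, or gives recruitment to someone blind to it.

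The arm therefore appears to be known when recruitment begins. No single sentence says so, and Figs. 1 and 2, which could show the order, are not available.

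**2. Places per centre**

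4 officers × 3 caregivers = 12 per centre. 12 × 7 centres = 84, which is the per-arm target under Sample size. If more than 12 caregivers in a centre are eligible and willing, the statement that all eligible caregivers take part and the 4 × 3 assignment cannot both hold. No rule says who is taken.

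**3. The plan's own sample size**

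Inputs (Sample size): difference 18.44, SD 17.0, ICC 0.3, cluster size 10, power 90%, significance 5% (two-sided assumed).

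- n per arm before clustering = 2 × [17.0 × (1.960 + 1.2816) / 18.44]² = 17.86
- Design effect = 1 + (10 − 1) × 0.3 = 3.7
- 17.86 × 3.7 = 66.1, which needs 7 centres of 10, or 70 per arm

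The stated figure is reproduced.

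**4. Illustration of size**

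The documents give no bias figure, so the shift b is an assumption.

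- SE of the difference = 17 × √(2 × 3.7 / 70) = 5.53 points (clustering counted, no gain from baseline adjustment)
- 0.2 × 17 = 3.4 points and 0.3 × 17 = 5.1 points, which are 18% and 28% of 18.44
- With no true effect, the chance of a significant result is 1 − Φ(1.96 − b/SE) + Φ(−1.96 − b/SE)

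| Assumed shift b (points) | ICC 0.3, SE 5.53 | ICC 0.05 (assumed), SE 3.46 |
|---|---|---|
| 2 | 0.065 | 0.089 |
| 3 | 0.084 | 0.140 |
| 5 | 0.148 | 0.304 |
| 8 | 0.304 | 0.638 |

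The last column uses design effect 1 + 9 × 0.05 = 1.45 and SE = 17 × √(2 × 1.45 / 70) = 3.46. A larger trial lowers the SE but not b.

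**The case against.** The other side has a fair case, and parts of it stand.

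- **The order is inferred.** This stands. The missing figures might show consent before allocation. The text alone points the other way.
- **There are safeguards.** An external person randomises, assessors are blinded, reasons for refusal are recorded, baseline data are compared, and the analysis adjusts for the baseline outcome and can add covariates. These help. None acts on unmeasured differences between those approached and consenting in one arm and those in the other.
- **The size is assumed.** This stands. At the planning ICC, a shift of 3 to 5 points raises false rejection to between 0.084 and 0.148. That is material, but it shows what could happen and does not estimate what will.

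A reader might also infer four stronger things that the documents do not support.

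- *That randomisation gives no protection.* It still balances centres in expectation. The gap concerns selection within centres.
- *That officers will choose who fills the 12 places.* This arises only if more than 12 are eligible, and the article gives no count of eligible caregivers per centre.
- *That recruiting effort is four officers against two.* The control-group text introduces its GP and nurse as being similar to the intervention group, so this may be a conflict of wording. Intervention officers also carry the delivery work, so headcount does not measure recruiting effort.
- *That control staff trained early will dilute the contrast.* Neither the date nor the content of their training is given. Dilution is possible, but the text does not show it.

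**Conclusion.** The concern holds in a limited form. Followed as written, the plan lets staff who know the allocation identify and enrol caregivers, and in intervention centres those staff also deliver the programme. Randomisation of centres does not protect against arm-dependent identification and consent within them, and the planned safeguards offset this only in part.

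The conclusion about order rests on reading the sections together without the two figures. The size cannot be derived. The 3.4 to 5.1 points against an SE of about 5.5 depend wholly on an assumed residual difference of 0.2 to 0.3 SD. The change is worth making because it is cheap before enrolment and impossible afterwards. Trial status puts the start of recruitment at the end of December 2021, after publication.

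**What to change.** 1. In all 14 centres, build the list of eligible caregivers from records and referrals, obtain consent and complete T-0 before the external biostatistician releases the allocation. Then train the intervention-centre officers in ITBCS and start the programme. While no arm is known, recruitment cannot differ by arm.
2. Where more than 12 are eligible in a centre, draw 12 at random from the list, in both arms. This reconciles the all-eligible statement with the 4 × 3 assignment.
3. Time T1 to T3 in both arms from one common start date after allocation. This is needed because T1 is three months after baseline under Intervention but directly after the main programme under Variables and measurements. A gap between T-0 and programme start would pull these apart.
4. Reconcile the number of officers per centre between Train the trainer and the control-group section. State that control-centre officers receive ITBCS skills training only after T-3.
5. Report numbers screened, eligible and consenting by centre and arm.

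Sections to amend: Recruitment, Randomization and allocation concealment, Intervention and Table 1, Train the trainer, Treatment as usual for the control group, Variables and measurements, and Intervention fidelity.

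The cost is wording and scheduling: a short delay between T-0 and programme start, and a later start for centres that finish recruiting early.

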#### Treatment as usual for the control group

Participants in the control group will not receive the ITBCS program during the intervention phase. They will continue with usual services available for them during this period without any restriction (usual care). From our previous study in this population, very few family caregivers receive any support outside their family in rural China, so we do not expect this to influence the study outcome. Similar to the intervention group, One GPs and one RN from each community health service center in the control group will be trained as project field officers. Their responsibilities will include: (1) participants recruitment; (2) making telephone reminder calls for the four time-point measurements; and (3) delivering the ITBCS program to participants in the control group after completion of the present study. The participants will complete the same measurements at the same time points as the ITBCS group.

Upon completing the 15-month study, all participants will receive a “thank you” letter for their participation in the study. The study flowchart is displayed in Fig. 2.

**Fig. 2 Fig2:**
[figure not shown]
Flowchart of the study

### Variables and measurements

Outcomes will be measured in both groups at baseline (T-0), immediately after main ITBCS (T-1), 9 months post-intervention (T-2), and 15 months post-intervention (T-3). Research assistants blinded to the group assignments will be responsible for collecting all the measures employed in the proposed study.

#### Primary outcomes

The primary outcome measure is family caregivers’ perceived burden at 15 months follow-up adjusted for baseline value.

#### Secondary outcomes

Secondary outcomes are the followings adjusted for baseline value: (i) family caregivers’ depressive symptoms; (ii) family caregivers’ social support; (iii) family caregivers’ caregiving self-efficacy; (iv) care recipients’ difficult behaviours; and (v) care recipients’ competence in activities of daily living.

#### Instruments

Table 4 shows the measurements and their relationship to outcomes and hypotheses of the proposed study.

**Table 4 Tab4:** Instruments used for outcome assessment

Categories	Instruments description	Hypothesis & description
Primary outcome	Zarit Burden Interview (ZBI): This 22-item scale is used to assess the self-perceived burden by caregivers for providing care to impaired elderly. All items are related on a 5-point scale. The response range is 0 (never) to 4 always, with higher scores indicating higher perceived burden. Cronbach’s alpha of the Chinese version is 0.89 [33].	The ITBCS will reduce the subjective burden of family caregivers.
Secondary outcome	Centre for Epidemiologic Studies Depression Scale (CES-D): This 20-item scale measures the frequency of common depressive symptoms. The response range is 0 to 3. Higher scores indicate more severe depressive symptoms. Cronbach’s alpha of the Chinese version is 0.85 [34].	The ITBCS will reduce the depressive symptoms of family caregivers.
	12-item Short-Form Health Survey (SF-12): This 12 question instrument will be used to assess health-related quality of life by eight sub-scales. Cronbach’s alpha of the Chinese version is 0.910 [35].	The ITBCS will improve the health-related quality of life of family caregivers.
	Social Support Rating Scale (SSRS): This 10-item scale is used to assess objective support, subjective support, and utilization of support on a 7-point scale. A higher score indicates higher levels of social support. SSRS is in the Chinese version. Cronbach’s alpha is 0.94 [36].	The ITBCS will improve the social support of family caregivers.
	Revised Scale for Caregiving Self-Efficacy (RSCSE): This scale includes three subscales to assess caregivers’ beliefs about their ability to address caregiving challenges. The score ranges from 0 (cannot do at all) to 100 (certainly can do). Cronbach’s alpha of the Chinese version for the three subscales is 0.92,0.95 and 0.86 respectively [37].	The ITBCS will improve the self-efficacy of family caregivers in providing care.
	Neuropsychiatric Inventory-Q (NPI-Q): This scale is used to measure the severity of behavioural and psychological symptoms of dementia (BPSD). A higher score indicates the more severe the BPSD and the higher caregiver distress level. Cronbach’s alpha of the Chinese version is 0.851 [38].	The ITBCS will reduce the difficult behaviours of people with dementia.
	Disability Assessment for Dementia (DAD): This scale is used to assess functional disability in people with dementia. Through an interview, caregivers are required to indicate the actual performance of the people with dementia in functional tasks over the previous 2 weeks with responses of “no”, “yes”, or “not applicable”. A higher score indicates less functional disability while a lower score indicates more dysfunction. Cronbach’s alpha of the Chinese version is 0.91 [39].	The ITBCS will improve competence in ADLs of people with dementia.

